**STUDY POPULATION**

**Inclusion Criteria**

Patients must meet all of the following criteria to be eligible for enrollment:

- Age ≥18 years
- Admission to the SICU or MICU for ≥ 72 hours and expected to stay and additional 48 hours
- IV access for administration of study drug
- Subject (or subject’s legal representative) able to give written informed consent

**Exclusion Criteria**

Individuals who have one or more of the following criteria will not be eligible for participation:

- History of hypersensitivity or intolerance to echinocandin antifungals
- Liver function test (ALT, AST, and/or total bilirubin)greater than 10 times the upper limits of normal (ULN)
- Pregnant or lactating women
- Treatment with systemic antifungal therapy within the preceding 7 days
- Documented IFI at baseline/screening
- Life expectancy less than 2 days or moribund

**CONSENT PROCESS**

Any one of the primary investigators may conduct the consent process. If the potential subject is awake, alert, and able to engage in discussion, the process will occur in the subject’s room. If the potential subject is sedated and/or unable to actively engage in the consent process for other reasons, discussion will be held with a legal representative, either in the subject’s room or in a private family conference room in the SICU. Approximately 30 minutes will be allocated for conducting the consent process, but may vary depending on the number or questions posed to the investigator. The subject or their surrogate will have up to 48 hours to consider whether or not to participate.

**Subject’s capacity to give legally effective consent**

A potential study subjects may not have the capacity to provide legally effective consent. Diminished capacity will not be assessed formally, but rather should be a reasonable clinical judgment made by the ICU care providers in conjunction with the study team. Factors to be considered include the subject’s mental status, sedative medications, and comfort level. These factors should be assessed by medication review and talking to the subject. Weekly reassessments of the subject’s capacity to give consent must be made. If a surrogate provided the initial consent, the subject should be reconsented as soon as their decisional capacity improves.

**STUDY MEDICATION**

**Rational for Dose Selection**

Subjects in the active surveillance arm who develop a single positive BDG test will receive preemptive anidulafungin intravenously. Preemptive therapy will include a loading dose of 200mg followed by 100mg maintenance therapy once a day. The loading and maintenance doses are derived from the FDA cleared schedule for IC and candidemia. No dosage adjustments are necessary for patients with hepatic or renal insufficiency, however, patients with LFTs ≥10 times ULN will be excluded from study participation. Isolated cases of hepatic dysfunction, hepatitis, or worsening hepatic failure have been reported in patients receiving anidulafungin, but a causal relationship to the drug itself has not been established.

**Duration of Preemptive therapy**

Preemptive therapy will continue until one of the following occurs:

1. A minimum of 14 days therapy (standard treatment duration for IC and/or candidemia*)*
2. Patient develops a proven or probable breakthrough IFI while receiving study drug (see appendix A for IFI criteria)
3. Patient develops unacceptable toxicity
4. The clinician or PI decides that it is not in the patients best interest to continue
5. Patient declines further study participation
6. Patient has received preemptive therapy for 28 days and has not yet been discharged from the SICU

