**Hypotheses:**

**1)** Biweekly β-D-glucan surveillance will identify SICU patients with an invasive fungal infection (IFI) before clinical signs or symptoms develop.

1. Anidulafungin initiated in response to a positive β-D-glucan test (i.e. preemptive therapy) will be well tolerated, safe, and effectively treat patients early, before advanced infection is established.
2. Peripheral blood gene expression signatures obtained serially from at-risk patients can predict early IC.

**Study Design:** Single center, randomized, non-blinded, parallel group, comparative study.

**Sample Size:** 100 subjects; 75 in the active surveillance/preemptive therapy arm and 25 in the usual care arm.

**Study Population:** Adult patients admitted to Duke University Medical Center SICU at-risk for the development of IC.

**Study Drug:** Intravenous anidulafungin initiated in response to a positive β-D-glucan test for subjects in the active surveillance/preemtpive arm. Preemptive treatment will continue for at least 14 days or until ICU discharge (maximum 28 days), which ever is longer.

**Efficacy:** IFI assessments will be made weekly and at SICU discharge.

**Safety:** A data safety monitoring board will review adverse events every 4 months.

**Statistics:** β-D-glucan test characteristics will be described using sensitivity, specificity, positive and negative predictive values. The proportions of patients developing proven or probable IC in each group will be compared using Fisher’s exact test. The prevalence of treatment emergent adverse events will be described using summary statistics. For gene expression analysis, we will designate subjects diagnosed with a *Candida* bloodstream infection as case patients and those who remained uninfected and had negative B-D-glucan testing as controls. Decision tree analysis will be used to develop predictive signatures for candidemia versus no infection.

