^h^ Hybridization to microarrays will occur in selected patients with positive blood culture results (cases) and in controls (no positive blood cultures, no empiric antifungal therapy).

^i^Two sets of blood cultures will be obtained within 24 hours of a positive BDG test result if not already collected as a part of clinical care.

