**Active surveillance/ preemptive therapy group**

Subjects in this arm of the study will have serum drawn twice a week for BDG testing while in the SICU, with the results of the test reported to the managing clinicians in real-time. Subjects will receive intravenous (IV) anidulafungin should the β-D-glucan exceed 60 pg/ml on a single determination. A positive test cut-off of 60 pg/ml was selected based on the observation that 81% of patients with IC will have a positive test at this level(25). Preemptive therapy will continue for a minimum of 14 days or for as long as the subject remains in the ICU up to a maximum of 28 days duration.

If the BDG test turns positive and preemptive therapy is initiated, serum will then be collected every other day to assess the kinetics of the BDG test on anidulafungin treatment. Kinetic monitoring will continue until the test becomes negative at which time twice weekly assessments will be resumed and continue for as long as the patient remains in the SICU. Samples collected while patients are receiving anidulafungin will be batched and run retrospectively. Clinicians will not have these results made available for use in real-time. However, once preemptive anidulafungin therapy is completed and the drug has been stopped, biweekly monitoring with results reported to the medical team will be resumed. Subjects, however will not be restarted on anidulafungin should the test again turn positive after a course of preemptive therapy is completed.

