**Drug Administration**

Study drug will be administered through IV infusion by nursing personnel according to the package insert. The rate of infusion will not exceed 1.1 mg/minute. If a study participant is discharged from the hospital prior to completion of preemptive therapy (minimum 14 days of treatment), they may have the study drug discontinued or continue daily administration of study drug by a visiting nurse at the discretion of their care provider. The sponsor will provide study drug to complete a total of 14 days, but will not cover the cost of home health care/infusion.

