**INITIATION OF PRE-EMPTIVE OR EMPIRIC THERAPY**

- APACHE II score recalculated based on laboratory and clinical features in preceding 24 hours (http://www.sfar.org/scores2/apache22.html).
- Complete physical examination including vital signs will be obtained within 72 hours of study drug initiation.
- Assess and document whether patient meets EORTC/MSG criteria for proven or probable IFI.
- Laboratory evaluation (LFTs will be obtained if not already done in preceding 3 days).
- Oral wash or ETS for semi-quantitative fungal culture with susceptibility testing will be performed.
- Supporting evidence of IFI obtained as part of routine care will be documented.
- Positive BDG test will prompt two sets of blood cultures to be obtained within 12 hours, if not already collected a part of routine care. Culture results will be made available for clinical care.
- Concomitant medications will be documented.
- AEs will be recorded.

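### The stopping list for preemptive therapy conflicts with the synopsis and design section on course length, and the blood-culture window and test cut-off are each stated two ways

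*Protocol*

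**What the plan says.** **Course length.** The synopsis (Study Drug entry) reads "Preemptive treatment will continue for at least 14 days or until ICU discharge (maximum 28 days), which ever is longer". The Active surveillance/preemptive therapy group section gives the same 14-day minimum, ICU-stay extension and 28-day maximum. The section headed Duration of Preemptive therapy is a list of six events introduced by "Preemptive therapy will continue until one of the following occurs". Item 1 is "A minimum of 14 days therapy" and item 6 is "Patient has received preemptive therapy for 28 days and has not yet been discharged from the SICU". Items 2 to 5 cover breakthrough infection, toxicity, a clinician or investigator decision, and patient refusal. Drug Administration adds that a patient who leaves hospital before finishing the minimum course may stop or go on at home, and that "The sponsor will provide study drug to complete a total of 14 days".

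**Blood cultures after a positive BDG.** Footnote i of the Chart of Study Procedures says "Two sets of blood cultures will be obtained within 24 hours of a positive BDG test result". The section on initiation of pre-emptive or empiric therapy says "Positive BDG test will prompt two sets of blood cultures to be obtained within 12 hours".

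**Cut-off.** The design section triggers anidulafungin when BDG exceeds 60 "pg/ml on a single determination". Diagnostic Tests defines a positive result as 60 pg/mL or more.

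**The concern.** A minimum cannot serve as a stopping event. If the first listed event ends therapy, reaching day 14 ends it, and nobody can meet the 28-day item. ICU discharge after day 14, which ends a longer course in the synopsis and design section, is not on the list at all. Someone dispensing from the duration section could stop at day 14, while someone working from the synopsis would continue for a patient still in the ICU.

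Several planned measurements hang on that date:

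- LFTs and physical examination are weekly while on anidulafungin, so the on-drug monitoring period follows course length.
- Clinical response (Table 5) and the end-of-therapy fungal culture are taken when treatment ends.
- Antifungal utilization and cost are secondary endpoints.
- The design section withholds BDG results while the patient is on anidulafungin and resumes real-time reporting once the drug is stopped. For a patient in the ICU on days 15 to 28, the duration rule therefore decides whether clinicians see the result.

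The culture window and cut-off are smaller mismatches of the same kind: one act can comply with one section and deviate from another.

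**Working it through.** **The protocol's own figure.** The Sample Size section expects 25% of 75 surveillance patients to turn positive: 75 × 0.25 = 18.75, rounded to the stated 19 treated. It reproduces.

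**Course length under each reading.** Let L be the ICU days after starting anidulafungin.

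- Stopping list, item 1 read literally: 14 days, absent an earlier event.
- Synopsis and design section: min(28, max(14, L)) days, absent an earlier event.

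The stated schedule (200 mg once, then 100 mg daily) is used only to convert days to cumulative drug: mg = 200 + 100 × (days − 1). The protocol gives no length of stay, so the values of L are assumptions chosen to show the range.

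| Assumed L | List, literal | Synopsis/design | Ratio, days | Ratio, mg |
|---|---|---|---|---|
| 14 or less | 14 | 14 | 1.00 | 1.00 |
| 18 | 14 | 18 | 1.29 | 1900/1500 = 1.27 |
| 21 | 14 | 21 | 1.50 | 2200/1500 = 1.47 |
| 28 or more | 14 | 28 | 2.00 | 2900/1500 = 1.93 |

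The largest gap for one patient is 28 − 14 = 14 drug-days, or two further weekly rounds of LFTs and examination. Over those two weeks the twice-weekly schedule yields about 2 × 2 = 4 BDG results, assuming the patient is back on that schedule. They are reported in real time under one reading and withheld under the other.

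**Trial-level bound.** 19 × 14 = 266 and 19 × 28 = 532 patient-days. The second figure needs all 19 patients to remain in the ICU for at least 28 days after starting. The first is not a floor either, since items 2 to 5 and the hospital-discharge provision can end a course sooner.

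**Culture window.** 24 hours against 12 hours, for the same two sets and the same trigger. A draw between 12 and 24 hours complies with the chart and deviates from the initiation section. It matters only where cultures were not already taken in routine care.

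**Cut-off.** Above 60 and at least 60 disagree at one value, exactly 60 pg/mL.

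**What does not change.** The safety analysis includes everyone who received at least one dose, whatever the course length. The feasibility definition names adherence to the surveillance protocol, off-schedule BDG orders, and antifungals started despite a negative BDG. All three can still be counted. They depend on the cut-off only at exactly 60.

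**The case against.** The best defence is that a minimum is not a cap. Item 6 presupposes courses beyond day 14, and the synopsis and design section agree with each other, so a careful reader could treat the list as clumsy drafting. That is fair as a reading of intent. But it means overriding the literal wording of the section that governs duration, and the list still lacks ICU discharge. These are rules of conduct, not details usually left to a statistical analysis plan.

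Three stronger readings are tempting, and the protocol does not support them.

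- *The feasibility endpoint cannot be scored.* Its named components survive, as shown above, and the analysis is descriptive. Only the broader term in the Feasibility Analysis paragraph, adherence to the preemptive protocol, becomes partly ambiguous if it is taken to include the treatment course and the triggered cultures.
- *The safety denominator changes.* It does not. Exposure time and the on-drug monitoring period change.
- *Exposure across the trial is uncertain two-fold.* That is an extreme bound, resting on an ICU stay that the protocol nowhere gives for any patient, let alone for all 19.

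Nor is the 14-day supply statement a further conflict. It concerns patients already out of hospital, hence out of the ICU, for whom the longer-of rule gives 14 days as well. Discretionary stopping there is an explicit exception, though the duration section does not mention it.

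**Conclusion.** The contradictions are in the current text. The duration section conflicts with itself and with the synopsis and design section. The consequence falls on patients still in the ICU after day 14: up to 14 drug-days each, a ratio between 1.0 and 2.0 depending on an ICU stay that has to be assumed. It reaches exposure time, the weekly safety-monitoring period, the timing of response and colonization assessments, antifungal use and cost, and BDG reporting on days 15 to 28. It leaves the safety population and the named feasibility components intact. The culture-window conflict is genuine but narrower, and the cut-off conflict is minor. Which clinical rule is right is not judged here.

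**What to change.** - Reconcile the stopping list with the synopsis and design section so that one duration rule appears throughout, with each listed event able to operate or else removed.
- State the hospital-discharge provision of Drug Administration in that rule as an explicit exception.
- Reconcile the culture window between chart footnote i and the initiation section, and the cut-off between the design section and Diagnostic Tests.
- If course completion or culture timing is to count as protocol adherence, say so and score it against the reconciled rules.

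The choice of clinical rule belongs to the investigators and sponsor. The cost is a short protocol amendment; no change to sample size or analysis method follows from it.

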**Drug Supplies**

Anidulafungin is manufactured by Pfizer, INC. Study drug will be provided by Pfizer, packaged in a single unit pack containing a vial of sterile, lyophilized, preservative-free powder (one 100mg vial) and a 30 ml diluents vial. The study drug supply will be maintained in the Duke University Medical Center Investigational Drug Pharmacy until administration. Storage will be as per the package insert. The medication will be reconstituted, mixed, and dispensed by the study pharmacist as directed on the product label. The pharmacist will be responsible for maintaining a dispensing log and receiving used bottles returned by nursing personnel after study drug administration.

**Drug Labeling**

Each bottle of study medication will be labeled with the study protocol number, drug name, strength, and batch number. Spaces will be provided for recording the patient’s initials, study ID number, date of dispensing, and amount to be administered.

**Drug Administration**

Study drug will be administered through IV infusion by nursing personnel according to the package insert. The rate of infusion will not exceed 1.1 mg/minute. If a study participant is discharged from the hospital prior to completion of preemptive therapy (minimum 14 days of treatment), they may have the study drug discontinued or continue daily administration of study drug by a visiting nurse at the discretion of their care provider. The sponsor will provide study drug to complete a total of 14 days, but will not cover the cost of home health care/infusion.

**Drug Accountability**

The Investigators will maintain accurate records of dates, quantities, lots of product(s) received, to whom dispensed (patient-by-patient accounting), and accounts of any product accidentally or deliberately destroyed. The Investigators will retain all unused or expired product. At the conclusion of the study, all unused drug supplies will be returned to the sponsor. An overall summary of all drug supplies received, used, wasted, and returned will be prepared at the conclusion of the study.

**Concomitant Medications**

There are no drugs that are contraindicated with anidulafungin. However, for study purposes, other systemic antifungal agents including amphotericin products, azoles, and/or investigational antifungal drugs may not be given during study drug dosing. If a patient in the preemptive therapy arm requires one of these agents, the patient must be discontinued from the study.

**SCHEDULE AND DESCRIPTION OF STUDY PROCEDURES**

**Identification of Potential Study Subjects**

A waiver of HIPPA and consent will be requested from the Duke University Medical Center IRB to review the SICU patient census daily and identify adults who have been in the unit for at least 3 days and who are expected to stay for an additional 2 days.

**Stratification and Randomization**

Patients who meet inclusion/exclusion criteria and provide written informed consent will be stratified into 2 groups based on APACHE II score. Group 1 will have APACHE II scores ≤ 20 and group 2 > 20. Subjects within each APACHE II group will then be assigned to either active surveillance with preemptive anidulafungin based on a positive BDG test or standard care using a 3:1 randomization schedule (approximately 75 subjects in the preemptive group and 25 in the standard care group). The study coordinator will assign each patient to the next available randomization number which will be generated using randomization software. Patient study identification (ID) numbers will also be assigned sequentially starting with Patient No. 1. Dropouts will not be replaced.

**Screening/Baseline**

Procedures must be performed within 3 days prior to randomization:

- **Signed informed consent prior to the performance of any study-specific procedures.**
- Complete medical and medication history, including a prior antifungal therapy review.
- Complete physical examination including vital signs.
- Liver function tests will be drawn if not already done as a part of standard care in the preceding 3 days.
- Calculate APACHE II score (<http://www.sfar.org/scores2/apache22.html>)
- Oral wash or ETS for semi-quantitative fungal culture with susceptibility testing.
- B-HCG test for women of childbearing age if not already done as a part of standard care (<60 years old)

**At Randomization**

- Stratify by APACHE II score
- Concomitant medications will be recorded.
- A serum red-top tube for BDG testing (3.5 ml) and a PAX Gene tube (5 ml) for RNA analysis will be obtained. *The PAX Gene tube must always be collected second due to processing requirements.

**All Subjects**

The following procedures will be performed for all study subjects for the duration of the SICU stay:

- Serum red-top BDG and a PAX Gene tubes will be obtained 2 times/week (generally Monday and Thursdays) with the routine early morning blood work by the SICU nursing staff. Both phlebotomy tubes will be sent directly to the Duke Clinical Microbiology Laboratory. BDG results will be made available in real-time (within 24–72 hours) via a phone call directly to the clinician (surgical house staff and unit pharmacist) caring for the study subject assigned to preemptive therapy. BDG specimens obtained from patients assigned to empiric therapy (standard care) will be batched and tested at the end of study and the clinicians will not be made aware of the results. All RNA analyses will also be performed retrospectively for research purposes only.

*Patients in the active surveillance/preemptive therapy arm may have BDG testing performed on other days if the providers feel that the result would immediately impact initiation of antifungal therapy. The test will be available daily Monday through Friday.

- IFI assessments will be made weekly (EORTC/MSG criteria for proven or probable IFI will be applied [**Tables 3 & 4**]) and documented on the CRF.
- Supporting evidence of IFI obtained as part of routine care will be recorded weekly (i.e. routine laboratory testing, microbiology and blood culture results, imaging studies, biopsy reports) and documented on the CRF.
- Clinical risk factors for IC will be documented weekly (**Table 1**) and documented on the CRF.
- Factors known to be associated with false positive BDG tests will be documented weekly (**Table 2**) and documented on the CRF.
- Concomitant antimicrobials and immunosuppressive drugs will be documented weekly on the CRF.
- AEs will be recorded weekly and documented on a dedicated CRF.

**INITIATION OF PRE-EMPTIVE OR EMPIRIC THERAPY**

- APACHE II score recalculated based on laboratory and clinical features in preceding 24 hours (http://www.sfar.org/scores2/apache22.html).
- Complete physical examination including vital signs will be obtained within 72 hours of study drug initiation.
- Assess and document whether patient meets EORTC/MSG criteria for proven or probable IFI.
- Laboratory evaluation (LFTs will be obtained if not already done in preceding 3 days).
- Oral wash or ETS for semi-quantitative fungal culture with susceptibility testing will be performed.
- Supporting evidence of IFI obtained as part of routine care will be documented.
- Positive BDG test will prompt two sets of blood cultures to be obtained within 12 hours, if not already collected a part of routine care. Culture results will be made available for clinical care.
- Concomitant medications will be documented.
- AEs will be recorded.

